### Participants

The study sample will consist of 80 outpatients fulfilling criteria for a diagnosis of Schizophrenia or Schizophrenia Spectrum, Major Depressive Disorder with psychotic symptoms, or Bipolar I Disorder with psychotic symptoms according to DSM-5 criteria, who had never experienced psychotic symptoms prior to the current episode. The diagnosis of all participants will be carried out by physicians with extensive experience in the diagnosis of FEP.

Inclusion criteria are (1) age between 16 and 65 years at the time of first evaluation; (2) have been diagnosed with a first psychotic episode in the last year, with or without pharmacological treatment and/or psychiatric hospitalization; (3) presence of one or more traumatic events causing trauma related symptoms (Impact of Event Scale-Revised, IES-R >0 and Subjective Units of Distress, SUD >5); 4) ability to read and write in Spanish.

Exclusion criteria are: (1) acute suicidality; (2) presence of organic brain diseases; (3) previous trauma-focused therapy in the past 2 years.

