### Study Aim

The main outcome of this project is to analyze whether EMDR therapy, as an adjuvant to TAU, is effective in reducing relapses in patients with an affective or non-affective FEP and a history of comorbid psychological trauma associated with first hospital admission and/or previous stressful life events. A range of scales, highlighted below, will be used to determine changes in psychiatric symptoms (see *Instruments and Measures*).

The secondary outcome includes whether EMDR therapy, as an adjuvant to TAU, is effective in reducing psychiatric symptoms and post-traumatic stress symptoms, in improving the overall functionality and quality of life associated with health, as well as adherence to pharmacological treatment. A range of clinical scales will be used the evaluate changes from baseline (see *Instruments and Measures*).

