### Computation of Sample Size

The study aims to assess the relative efficacy of an EMDR intervention protocol for patients with FEP versus TAU mainly in terms of stabilization and clinical improvement, reduction of anxious, depressive, somatic and/or psychotic symptoms, among others. For this reason, the main variable used is the number of clinical relapses after the intervention, with a follow-up of up to 12 months. Using previous studies as a basis (33), the sample size has been calculated based on a survival analysis with the statistical package “powerSurvEpi” for R, (http://www.r-project.org/) using an alpha = 0.005 instead of 0.05 to allow correction for multiple comparisons. The number of patients required to detect a hazard ratio = 2 in a Cox regression with a statistical power of 80% and alpha = 0.005 is n = 36 per intervention group (two groups, total n = 72). According to Chambless and Hollon (29), a sample of this size should show clinically relevant differences. Assuming a loss percentage of approximately 10–15% of the patients in the study, it would be necessary to recruit approximately 80 patients, 40 for each branch of intervention.

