Suicide Module of Mini-International Neuropsychiatric Interview (MINI) (47): This is a short structured diagnostic interview, validated in Spain (48), which assesses the risk of suicide.A diagnosis of substance use disorder will be made according to DSM-5 criteria; the alcohol abuse and dependence and substance abuse and dependence modules of the MINI will also be used to determine diagnosis (48).Beck Depression Inventory (BDI-II): The BDI-II (49, 50), Spanish validation (51), is a 21-item clinician-administered scale designed for use with patients with a prior depression diagnosis, to quantitatively assess changes in the severity of depressive symptoms. Scores are summed and the total score indicates: 0–13 minimal depression; 14–19 mild depression; 20–28 moderate depression and 29–63 severe depression.Young Mania Rating Scale (YMRS): The YMRS (52), Spanish validation (53), is an 11-item clinician-applied scale which quantifies the severity of manic and hypomanic symptoms. Four items are given more weight to compensate for a lack of cooperation in acute patients and are graded on a 0 to 8 scale (irritability, speech, thought content and disruptive/aggressive behavior), while the remaining seven items are scored from 0 to 4. The scores are interpreted as follows: ≤12 indicates remission; 13–19 indicates minimal symptoms; 20–25 indicates mild mania, 26–37 indicates moderate mania and 38–60 indicates severe mania.Positive and Negative Symptom Scale (PANSS): The PANSS (54), Spanish validation (55), is an 30-item clinician-administered scale which measures positive, negative and general psychopathological symptoms on a scale of 1–7, based on the severity of the symptom. The semi-structured sci-PANSS interview (56), available in Spanish, will be used to facilitate the PANSS score.Global Assessment of Functioning Scale (GAF): The Spanish validation version of the GAF, which uses the acronym EEAG (57), is a brief measure of overall psychological disturbance, providing a global score ranging from 0 to 100. The lower the score, the poorer the functional status.

**Table 3 T3:** Measurements to evaluate diagnosis, clinical symptoms, and functionality.

Clinical variable	Measurement interview/self-report	T0 baseline	T1 Post-treatment 6 months	T2 Post-treatment 12 months
Diagnosis suicide	MINI	x		
Diagnosis S.	MINI	x		
Depression	BDI-II	x	x	x
Mania	YMRS	x	x	x
Psychotic S.	PANSS	x	x	x
Functionality	GAF	x	x	x

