
## Limitations

One limitation of this study is the inclusion of both affective and non-affective FEP, as well as comorbid substance use disorders, leading to a more heterogeneous sample. These inclusion criteria were decided on to ensure the study was carried out on a representative real-world population. We suggest this limitation can be addressed by matching the samples in both arms. Additionally, the main underlying clinical variable common to all patients is the presence of comorbid psychological trauma. Another potential source of bias is the lack of control regarding pharmacological treatment. To partly overcome this limitation, a ‘pharmacological treatment’ variable will be included and, to the extent it is possible, patients in the study should not have their drug therapy altered once they are stabilized. As our unit has extensive experience in treating FEP patients and uses standardized treatment protocols, this will also help limit this as a potential source of bias.

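### Entry does not require the first episode to have remitted or stabilised although the main outcome is relapse, so relapse may be mixed with persistence of the index episode; the size of the effect is unknown

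*Protocol article*

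**What the plan says.** The Study Aim asks whether EMDR added to usual care "is effective in reducing relapses in patients with an affective or non-affective FEP". Relapse is also the first hypothesis, and Computation of Sample Size states that "the main variable used is the number of clinical relapses after the intervention, with a follow-up of up to 12 months".

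Participants opens with "The study sample will consist of 80 outpatients fulfilling criteria for a diagnosis of Schizophrenia or Schizophrenia Spectrum" and limits these to patients "who had never experienced psychotic symptoms prior to the current episode". The second inclusion criterion is to "have been diagnosed with a first psychotic episode in the last year, with or without pharmacological treatment and/or psychiatric hospitalization". The other inclusion criteria concern age, trauma symptoms (IES-R above 0 and SUD above 5) and literacy in Spanish. The exclusions read: "Exclusion criteria are: (1) acute suicidality; (2) presence of organic brain diseases; (3) previous trauma-focused therapy in the past 2 years". No item in either list sets a symptom ceiling, a remission state or a period of stability.

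Two other places touch on stability. Computation of Sample Size names stabilisation among the things the intervention is meant to achieve. Limitations says that, as far as possible, "patients in the study should not have their drug therapy altered once they are stabilized".

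PANSS, YMRS and BDI-II are taken before allocation (Tables 1 and 3). The biased coin balances age, sex and years of education (Randomization Procedure). Statistical Analysis allows variables that turn out significant to serve as covariates in logistic or linear regression. A Cox model appears only in the sample-size section.

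**The concern.** A relapse is a return of illness after improvement. The eligibility list is printed in full and sets thresholds for trauma, but sets none for the state that the main endpoint presupposes. A patient diagnosed recently, never admitted, untreated and still symptomatic meets every criterion. For that patient, a later deterioration or admission may reflect an index episode that never resolved.

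Three things are at stake:

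- **Interpretation.** The result may not be purely about preventing relapse.
- **Dilution or lost events.** Which of the two occurs depends on how such patients are scored.
- **Chance imbalance.** With 80 patients, baseline severity can differ between arms, because the allocation procedure does not act on it.

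**Working it through.** **The plan's own figures.** The only planned figures used here are the hazard ratio (HR) of 2 and the 36 patients per group. The point does not depend on whether the sample size is right. For the record, it does not reproduce. At two-sided alpha 0.005 and 80% power, Schoenfeld's formula gives 4 × (2.807 + 0.842)² / (ln 2)² = 111 events, more than the 72 patients. That is a separate matter.

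**Assumptions, none given in the documents.** TAU relapse by 12 months among remitted patients is p = 40% (range 30–50%). Relapse times are exponential. The HR, TAU against EMDR, is 2 among remitted patients. A share f = 10%, 20% or 30% is non-remitted at T0.

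**Hand check, non-remitted patients scored as relapsed in both arms.** EMDR risk among remitted patients is 1 − (1 − 0.40)^(1/2) = 0.225. Each arm's observed risk is f + (1 − f) × risk.

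| f | TAU | EMDR | Risk ratio |
|---|---|---|---|
| 0 | 0.40 | 0.225 | 1.77 |
| 10% | 0.46 | 0.303 | 1.52 |
| 20% | 0.52 | 0.380 | 1.37 |
| 30% | 0.58 | 0.458 | 1.27 |

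**Cox HR by simulation** (400,000 patients per scenario, 12-month horizon, read to about ±0.03). In the first three columns every non-remitted patient has an event at a uniform time in months 0–6, whatever the arm. The columns differ in when counting starts, among patients event-free until then. In the last column these patients never have an event.

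| f | From randomisation | After month 5 | After month 6 | Never scored |
|---|---|---|---|---|
| 10% | 1.68 | 1.88 | 2.00 | 1.97 |
| 20% | 1.51 | 1.77 | 2.00 | 1.95 |
| 30% | 1.37 | 1.67 | 2.01 | 1.92 |

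Over p = 30–50%, counting from randomisation gives 1.61–1.74, 1.40–1.56 and 1.31–1.44. Counting after month 5 gives 1.83–1.90, 1.69–1.82 and 1.60–1.73. The residual loss after month 5 arises only because one sixth of the assumed non-remitted events fall between months 5 and 6.

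**Events lost if never scored.** Expected events with 36 per group are 36 × (0.40 + 0.225) × (1 − f). This gives 22.5 at f = 0, then 20.3, 18.0 and 15.8, a loss of 10%, 20% and 30%.

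**Chance imbalance.** Suppose 16 of 80 patients are non-remitted and the split is a random 40/40. The hypergeometric probability that the arms differ by 4 or more is 0.40. If all are scored as relapsed, the balanced risk difference is 0.52 − 0.38 = 0.14. With 10 in TAU and 6 in EMDR it is (0.25 + 0.75 × 0.40) − (0.15 + 0.85 × 0.225) = 0.55 − 0.34 = 0.21. With the reverse split it is 0.49 − 0.42 = 0.07.

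**The case against.** The case for leaving entry as it is has force, and several parts of it stand.

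- **The phrase about the current episode defines first-episode status.** It says that there was no earlier psychosis. It does not say that patients are actively psychotic at T0. The sample is described as outpatients, and the TAU section starts usual care after hospital discharge. A reader might infer that many patients enter unremitted, but the documents do not show this. Equally, outpatient status is a setting and not remission, and discharge does not apply to patients who were never admitted.
- **The relapse definition is not printed.** A reader might infer that non-remitted patients either cannot relapse or are scored as relapsing regardless of arm. Neither follows. If relapse means admission or marked worsening, a symptomatic outpatient can have the event, at a rate that may differ by arm.
- **The counting window matters.** The sample-size section counts relapses after the intervention, and Dropouts and Follow-Up removes patients admitted after a relapse during the 5-month treatment period. On that reading most of the dilution disappears. Hypothesis 1, which also compares relapses at T1, leaves the window ambiguous.
- **Broad entry affects both arms alike in expectation.** The comparison remains valid for outpatients with a recent first episode.
- **A remission requirement at entry has real costs.** At 10–30%, it would remove 8–24 of 80 patients. It would leave less room to show the symptom reduction in Hypothesis 2. It is also a clinical rule. Counting relapse only after a documented remission would be hard to apply, because PANSS and YMRS are scheduled only at T0, T1 and T2.

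What remains is that entry, stabilisation wording and endpoint do not fit together, and that baseline severity is neither balanced nor prespecified for adjustment.

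**Conclusion.** The concern holds in a limited form. The protocol fixes an eligibility list with no remission or stability condition, makes relapse its main outcome, and elsewhere allows for stabilisation after entry. The relapse result may therefore include persistence of the index episode.

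How much this matters cannot be determined from the documents. The fall of an HR of 2 to about 1.4–1.7 needs two assumptions together: 10–30% non-remitted, and all of them scored as relapsing from randomisation with no treatment effect. It is an upper illustration and not an expected loss. Under the post-intervention count the dilution is smaller or absent. If such patients are never scored, the HR is nearly unbiased and the cost is 10–30% of events. Chance imbalance in baseline severity is plausible in a trial of 80 under any definition that lets severity affect the event.

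This does not invalidate the randomised comparison. It bears on interpretation and precision.

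**What to change.** 1. Prespecify T0 PANSS as a covariate in the Cox model for relapse, in place of choosing covariates by their significance. The score is already collected before allocation, so adjustment keeps the randomised comparison. It addresses chance imbalance and recovers some precision. It does not by itself separate persistence from relapse.
2. Report a sensitivity analysis of relapse by T0 symptomatic status, using the T0 scales already taken. The trial team should set the grouping before unblinding.
3. Reconcile the entry criteria (Participants), the stabilisation wording (Computation of Sample Size, Limitations) and the relapse endpoint, so that persistence of the index episode is not counted as relapse. No clinical threshold is proposed here.

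The cost is one extra model term, a hazard ratio that is then conditional on T0 PANSS, and a small subgroup analysis with wide intervals. No new data, visits or patients are needed.

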The physiopathological mechanisms underlying the link between trauma and psychosis are not fully understood, but appear to be due to a complex interplay of trauma, genetic, epigenetic and environmental factors (4). Furthermore, the prevalence of posttraumatic stress disorder (PTSD) in psychosis was estimated at 12.4% in a meta-analysis of 20 studies (95% CI, 4.0–20.8%) (11). A diagnosis of PTSD in psychosis was associated with poorer social functioning and more severe psychiatric symptoms (12–14). Of particular note is that the experience of suffering a FEP in and of itself can constitute a highly stressful event which triggers symptoms compatible with PTSD: this clinical condition has been defined as post-psychotic post-traumatic syndrome (PPS) (15) and is estimated to occur in 40–80% of all FEP patients (16). A range of issues are potentially traumatic for FEP patients, from the experience of suffering psychotic symptoms, such as auditory hallucinations involving hearing voices, persecutory delusions or disorganized behavior, to the experience of being admitted to a psychiatric unit for the first time. This experience can involve involuntary hospitalizations and/or drug treatment, or other restrictive measures such as mechanical restraints, and is an important risk factor for traumatization (10), and is associated with feelings of anger, sadness, distrust or impotence. The risk of developing PPS following a FEP is increased in patients with prior childhood trauma (17). The presence of PPS is associated with an increased severity in psychotic symptoms (18) and concomitant clinical depression (19). Trauma hinders adherence to drug treatment (20), which is already particularly difficult in FEP patients in general (21). Thus, PPS has significant consequences at both prognostic and treatment levels (15).

All of this evidence suggests there is an urgent need to go beyond the treatment of psychotic symptoms and integrate trauma-focused psychotherapy into the care plan for FEP patients, especially in the high-risk period following hospitalization.

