### Randomization Procedure

After the baseline (T0) assessment (see later), we will randomly allocate participants to the EMDR or TAU group following a biased coin procedure (29). We want to note that in small clinical trials, simple randomization may lead to substantial imbalance in the relevant confounding factors between groups. The biased coin procedure attempts to balance these confounding factors but it still randomizes the patients and conceals their allocation (30). It has been included in the international guidelines for drug clinical trials (31) adopted by the European Community, Japan, United States FDA, Canada and Switzerland (32).

Specifically, a computer in a central location will allocate the patients as follows: (a) it will randomly allocate the first two patients to one group or the other with p = 0.5, (b) it will allocate the next patients as follows: (b1) if one group already includes at least two more patients than the other group, it will randomly allocate the patient allocated to the smallest group with p = 0.8, (b2) otherwise, it will first simulate that the patient is allocated to EMDR and calculate the sum of the between-group square standardized differences in age, sex and years of education, it will then simulate that the patient is allocated to TAU and recalculate the sum, and finally it will randomly allocate the patient to the group associated to the smallest sum with p = 0.8. Following this procedure, the final groups should be balanced in size and matched in age, sex and years of education. An independent researcher in a central location will control the computer program that will carry all steps of the randomization process.

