### Statistical Analysis

The distribution of socio-demographic, clinical (including psychological trauma), functionality, quality of life and treatment adherence characteristics among baseline groups will be analyzed using descriptive statistics. Continuous variables with a normal distribution will be analyzed with the Multivariate Variance Analysis. The change of the clinical variables of functionality and quality of life with respect to the baseline assessment at strategic points of the intervention will be analyzed by ANOVA with repeated measurements, including time factors, treatment conditions and their interaction. For those cases in which the premises of normality are not fulfilled, the Wilcoxon test will be used. The differences between groups, for the categorical and main clinical variables, will be analyzed by means of the Chi-square test. Those variables that are statistically significant can be used as covariates for a logistic or linear regression study of the factors associated to the magnitude of the effect and determine which variables are the best predictors of functioning. The effect size index (Hedges g or r de Pearson index) will be estimated in case of correlation indexes of each of the analyses performed. The statistical software used for the analyses will be the latest available version of the SPSS (v. 23).

For the main statistical analysis, we will conduct an intention-to-treat (ITT) analysis. We will impute lost to follow-up with the Last Observation Carried Forward (LOCF) method.

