#### TAU

Once patients are discharged from the hospital, they will be treated by the multidisciplinary team of the Intensive Early Intervention Programme for Incipient Psychosis (PAE-TPI) as part of their usual treatment, which consists of a multidisciplinary approach that includes pharmacological treatment and psychological support, as well as visits with social workers or nursing staff. An individual care plan is drawn up depending on the patient’s individual needs, which may include follow-up psychiatric visits to evaluate clinical status and, if necessary, readjust pharmacological treatment, and psychological visits to assess and detect risk situations and prevent relapses using a non-trauma focused CBT. The TAU psychological treatment will not under any circumstances be focused on PTSD or trauma symptoms.

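### Entry is open for a year after the first-episode diagnosis, but time since diagnosis is neither a balancing factor nor a named covariate: a minor loss of precision, not a bias

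*Protocol article*

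**What the plan says.** Inclusion criterion 2 (Methods, Participants) admits patients who "have been diagnosed with a first psychotic episode in the last year, with or without pharmacological treatment and/or psychiatric hospitalization". If T2 is counted from T0, the 12-month visit can therefore fall anywhere from about 12 to 24 months after diagnosis.

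The Introduction argues for adding trauma-focused therapy to care "especially in the high-risk period following hospitalization". The TAU section describes usual care from discharge onward: "Once patients are discharged from the hospital, they will be treated by the multidisciplinary team".

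The Randomization Procedure section gives its reason for a biased coin: "in small clinical trials, simple randomization may lead to substantial imbalance in the relevant confounding factors between groups". It then specifies the algorithm in full. After a rule on group size, step b2 sums the squared standardised differences in three variables, so that "the final groups should be balanced in size and matched in age, sex and years of education". No clinical variable is included.

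The Statistical Analysis section has one rule on covariates: "Those variables that are statistically significant can be used as covariates for a logistic or linear regression study of the factors". That regression concerns factors linked to the size of the effect and predictors of functioning, not relapse. The Limitations section adds a pharmacological treatment variable without saying how it enters the relapse analysis. Time since the episode is named in neither the allocation nor the analysis.

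**The concern.** Relapse is the main outcome, and relapse risk may well depend on how long ago the episode occurred. One patient may enter weeks after diagnosis and another at month 11. The article itself hints that timing matters and justifies its allocation method by the danger of confounder imbalance in a small trial, yet it balances demographic variables only. Choosing covariates by significance also differs from naming a plausible prognostic factor in advance.

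At stake are some precision in the relapse comparison and the ease of interpreting one estimate if the arms happen to differ in time since diagnosis.

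**Working it through.** The article gives no figure for time since diagnosis, so there is none to reproduce. The planned hazard ratio of 2 (Computation of Sample Size) serves only as a yardstick. The stated 36 per group at alpha 0.005 and 80% power could not be reproduced: the Schoenfeld formula needs 111 events two-sided, or 98 one-sided, from 72 patients. That is a separate and larger problem.

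**Inputs from the article:** 40 patients per arm; entry 0 to 12 months after diagnosis; hazard ratio 2.

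**Assumptions, not in the article:** entry uniform over the year; relapse hazard falling log-linearly by a factor R over the year, with R = 1.5, 2 or 4; for the simulation, about 40% relapse in controls by 12 months.

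**Step 1. Size of a chance imbalance.**
- SD of time since diagnosis = 12/√12 = 3.46 months.
- SE of the between-arm difference in means = 3.46 × √(2/40) = 0.77 months.
- 95% limit = 1.96 × 0.7746 = 1.52 months.

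**Step 2. Shift in the hazard ratio at that limit**, exp[(ln R / 12) × 1.518]:

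| R | Shift in log HR | Factor on HR | Share of ln 2 |
|---|---|---|---|
| 1.5 | 0.051 | 1.05 | 7% |
| 2 | 0.088 | 1.09 | 13% |
| 4 | 0.175 | 1.19 | 25% |

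**Step 3. Is there bias or inflation?** The article's biased coin was simulated with 80 patients and 1,500 runs per scenario, then analysed by Cox models without time since diagnosis. With no treatment effect, the rejection rate at nominal 0.05 was 0.053 (R = 2) and 0.040 (R = 4); the Monte Carlo SE is √(0.05 × 0.95/1500) = 0.006. The mean log HR was −0.008 and −0.007. There is neither bias nor inflation.

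**Step 4. What adjustment gains** (true HR 0.5, the same size as 2 on the log scale):

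| R | Power at 0.05, unadjusted → adjusted | Power at 0.005, unadjusted → adjusted |
|---|---|---|
| 2 | 0.379 → 0.384 | 0.087 → 0.096 |
| 4 | 0.365 → 0.393 | 0.085 → 0.089 |

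**Step 5. Share of the noise.** With no effect, the simulated SD of the log HR is 0.357 (R = 2) and 0.347 (R = 4). A one-SE imbalance contributes (ln 2/12) × 0.7746 = 0.045 or (ln 4/12) × 0.7746 = 0.089. The variance shares are roughly (0.045/0.357)² = 2% and (0.089/0.347)² = 7%. The small number of relapses, about 25 to 33 per simulated trial, dominates.

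**Step 6. Effect of balancing.** Adding time since diagnosis to step b2 cut the SD of the imbalance from about 0.77 to 0.30 months. At R = 4, balancing without the covariate left power at 0.364.

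**The case against.** The strongest reply is that every trial leaves some prognostic factors to chance, and that the test and confidence interval already allow for this. That stands: Step 3 shows it, and Step 4 shows that adjustment gains little. Affective or non-affective diagnosis, substance use and centre are also left out of the coin, and the article does not show that time since diagnosis matters more than these.

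The covariates of a relapse model often sit in an analysis plan, and none is shown. A reader might infer that the trial will not adjust; the article does not establish that. It does fix the balancing factors completely, and its one stated covariate rule is driven by significance.

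A reader might also infer much larger distortions. Split patients half early, half late: the SD of the between-arm difference in the early proportion is √(2 × 0.25/40) = 0.112, so the 95% limit is 22 points. With 2- or 3-fold hazards in early entrants, the rate ratio shifts by 1.61/1.39 = 1.16 or 2.22/1.78 = 1.25. The arithmetic is right, but neither the split nor the hazard factors come from the article. Under a log-linear gradient, a 2-fold ratio between the halves corresponds to a 4-fold fall over the year, and a 3-fold ratio to a 9-fold fall (3²). These are steep scenarios, taken at the extreme of chance.

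Finally, a reader might expect separate early and late estimates to show whether EMDR works in the high-risk period. They would not. The Introduction's clock starts at hospitalization, criterion 2 starts at diagnosis and admits patients never hospitalized, and a half-and-half split leaves about 20 patients per cell.

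**Conclusion.** The point holds as a minor matter of efficiency. The one-year entry window, the purely demographic biased coin and the significance-based covariate rule fit poorly with the article's own reason for balancing and its remark about a high-risk period.

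The consequence is small. The hazard ratio shifts by about 5% to 9% at the 95% limit of imbalance for a 1.5- to 2-fold gradient, and by about 19% for a 4-fold one. Power at 0.05 falls short by about half a point to three points. These sizes rest on uniform entry, a log-linear gradient and, for power, about 40% control relapse. The article supplies none of the three; its high-risk remark is qualitative and gives no relapse rate by time.

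A reader might conclude that the relapse result is biased or its error rate inflated. Random allocation rules that out, and the simulation agrees.

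**What to change.** State that months from first-episode diagnosis to T0 enters the relapse model as a continuous covariate, whatever its significance. This requires a regression model for relapse, such as the Cox model on which the sample size is based; the chi-square test named for the main clinical variables cannot carry a covariate. The diagnosis date is already needed to apply inclusion criterion 2, so no new data are required. The cost is one model term and a sentence in the analysis text. The adjusted hazard ratio is then conditional on time since diagnosis and can differ slightly from the unadjusted one (mean log HR −0.726 against −0.697 at R = 4 in the simulation).

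Optionally, for patients not yet randomised, add the same variable to the sum in step b2 and record the date of the change. This weakens balance on age, sex and education slightly. It should accompany the covariate, not replace it, because balancing alone gained no power. Eligibility need not change.
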